### Data collection and follow-up

Screening/baseline assessments include general demography and relevant medical history, including prior/concomitant therapies and tumour assessment within the 4 weeks before randomization; complete physical examination and laboratory tests within 7 days before randomization. The SPIRIT flowchart of the trial can be found in Fig. 2. Outcomes will be blindly assessed, except for intra-operative measures.

**Fig. 2 Fig2:**
[figure not shown]
SPIRIT flowchart

All patients included will be followed up in accordance with the guidelines for patients operated on for CRC LM for up to 6 months post-surgery.

### Statistical considerations

#### Sample size

The study is powered to detect a clinically meaningful reduction in blood loss during hepatectomy in patients with LM. Assuming a blood loss of 7.6 +/− 3.7 mL/cm^2^ in arm B (data based on our own experience), the study will have 85% power to detect a twofold decrease of blood loss in arm A using a Wilcoxon (Mann-Whitney) rank-sum test with a 0.05 two-sided significance level.

Twenty-one randomized patients per arm are required, corresponding to a sample size of 42 patients. Due to the occurrence of potential contraindications to hepatectomy between enrolment and randomization at the beginning of surgery, up to 8 patients may be enrolled in addition to the 42 planned. Indeed, the expected overall number of recruited patients is 50, with an enrolment period of 24 months and an additional follow-up of 6 months after randomization of the last patient.

#### Analysis populations

The three following populations will be defined for statistical analysis:The intent-to-treat (ITT) population includes all randomized patients.The per protocol (PP) population will consist a subset of patients in the ITT population and includes all patients with no major protocol violation for inclusion and non-inclusion criteria and who are compliant with requirements of the study protocol.The safety population includes all patients who underwent the surgery.

All protocol deviations leading to exclusion from the ITT to the PP population will be detailed in the analysis plan.

#### Statistical analyses

Qualitative variables will be described using frequency and percentage distributions. The number of missing data will be given, but will not be considered for the calculation of proportions.

Quantitative data will be described using the number of observations, mean, standard deviation, median, minimum and maximum values.

Patient characteristics and other baseline data (demographics, disease characteristics, clinical and biological data) will be summarized. The date of randomization will serve as a reference for calculation of durations unless otherwise indicated.

All analyses will be performed using the SAS software v9.1 (SAS Institute Inc., Cary, NC, USA).

The primary endpoint will be analysed for the ITT and PP populations.

A Wilcoxon (Mann-Whitney) rank-sum test will be used to compare the normalized blood loss distribution between the two arms at a 5% level in a two-sided situation.

For secondary endpoints, data will be compared between the two arms using a Wilcoxon (Mann-Whitney) rank-sum test. The rate of positive margin and the rate of local recurrence will be summarized by a proportion together with their 95% confidence interval. Post-operative complications will be described by study arm and compared using a Pearson’s chi^2^ test or a Fisher’s exact test, if adequate.

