**Methods:**

This is a prospective, single-centre, randomized (1:1 ratio), comparative, open-label phase II study. Patients with LM requiring a hepatectomy for ≥ 2 segments will be included. Patients with cirrhosis or sinusoidal obstruction syndrome with portal hypertension will be excluded. The primary endpoint is normalized blood loss in millilitres per square centimetre of liver section plane. Secondary endpoints are: total blood loss, transection time, transection time per square centimetre of liver area, haemostasis time, clip density on the liver section area, rate and duration of the Pringle manœuvre, rate of patients needing a blood transfusion, length of hospital stay, morbidity, patients with positive resection margin, and local recurrence. Assuming a blood loss of 7.6 ± 3.7 mL/cm^2^ among controls, the study will have 85% power to detect a twofold decrease of blood loss in the experimental arm, using a Wilcoxon (Mann-Whitney) rank-sum test with a 0.05 two-sided significance level. Twenty-one randomized patients per arm are required. Considering the risk of contraindications at surgery, up to eight patients may be enrolled in addition to the 42 planned, with an enrolment period of 24 months. Randomization will be stratified by surgeon.

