### Study design

This is a prospective, single-centre, randomized, comparative, open-label, phase II study to evaluate the efficacy and the safety of HIFU-AR, using the device described, during an open liver resection in patients with LM.

Patients will be randomized 1:1 to either:arm A (experimental arm): pre-coagulation by HIFU-AR plus standard surgical liver resectionarm B (control arm): standard surgical liver resection.

The randomization will be performed via an Internet platform in the operating room and will be stratified by surgeon ([name]) to ensure equal allocation of subgroups of participants (i.e. to each surgeon) in each arm.

The flowchart is represented in Fig. 1. The Standard Protocol Items: Recommendations for Interventional Trials (SPIRIT) checklist can be found in Additional file 1.

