### Surgical procedure

Anaesthesia will be performed according to standard procedure. Central venous pressure (CVP) will be measured immediately before and after the transection. No pharmacological intervention (such as a diuretic) and no surgical procedure (such as infra-hepatic inferior vena cava clamping) will be used to modify the CVP.

The procedure begins with a full exploration of the abdominal cavity, liver palpation and intra-operative ultrasound to confirm the indication of liver resection. Hepatectomy will be carried out in the same way in the two study arms. In arm A, hepatectomy will be performed after pre-coagulation of the hepatic parenchyma by HIFU along the section plane. This will be the only difference between arm A and arm B. Whenever possible, selective control of inflow will be performed. Otherwise, the Pringle manoeuvre will be used if haemorrhage of more than 500 mL occurs during hepatectomy.

In arm A, pre-coagulation is intended to establish a defined full-thickness plane of coagulative necrosis. This is generally achieved by six to ten side-by-side 40-s HIFU ablations, though more can be used if necessary. Resection is performed in the middle of the pre-coagulated zone.

In both arms, parenchymal division will begin along line marked by electrocautery and then cut with scissors. Liver resection technique (the same for both groups) uses a Kelly clamp claw, a suction device, a bipolar forceps and metallic clips. Blunt clamp dissection is a rapid, easy and cheap method. In essence, a large Kelly clamp is used to crush the liver parenchyma. The relatively soft liver substance dissects away, leaving behind the vascular and biliary structures, which are then ligated by vascular clips.

In arm A, it is planned that all vessels < 5 mm in diameter are sealed successfully using HIFU pre-coagulation and will not require any additional haemostasis. Surgical clips will be used only to control the few vessels > 5 mm in diameter.

After completion of liver parenchyma section and removal of the resected liver, the surgeon will complete haemostasis of the raw surface of the remaining liver. This haemostatic phase will be performed only with Prolene® stitches (Ethicon Inc., Cornelia, GA, USA), or coagulation with electrocautery, bipolar forceps or Argon beam coagulator.

Any use of special haemostatic products [such as Tachosil® (Takeda Pharmaceutical Company Limited, Osaka, Japan) or biological glue] will be noted.

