## Discussion

Hepatic resection techniques have been improved using devices such as bipolar forceps, water jet dissectors, ultrasonic cutting systems, and Argon coagulation. These techniques are both expensive and time consuming. Recently, new approaches have been developed to allow bloodless hepatic resection without any vascular exclusion using energy sources such as radiofrequency, ultrasonic scalpels, and microwave coagulation [28–32]. Among these alternative techniques, the use of HIFU has potential advantages.

Preclinical study has demonstrated that HIFU-AR using the new toroidal-shaped transducer during an open procedure in an animal model is safe, reduces bleeding, and can be guided by real-time ultrasound imaging. This work demonstrated blood loss reduction during hepatic resection without the Pringle manœuvre (hepatic pedicle clamping). This was avoided where possible to prevent liver ischemia–reperfusion injury, which is known to predispose patients to post-operative liver failure. In addition, it showed the feasibility, safety, and reproducibility of HIFU-AR during an open procedure. This technique also holds promise in human patients for whom pre-coagulation may offer better control of blood loss, especially in a liver fragile following chemotherapy. Patients undergoing iterative hepatic resection might also benefit from HIFU pre-coagulation. The sample size was calculated to have a twofold decrease in blood loss, because we consider this twofold decrease clinically relevant and in accordance with the results observed in the preclinical study (11.35 mL/cm^2^ versus 4.77 mL/cm^2^). The value chosen for the sample size calculation (7.6 mL/cm^2^ in the control arm) is in the upper limit of reported blood loss in the literature. It is based on personal data when measuring blood loss was determined by aspirated fluid and also by weighing all blood-soaked surgical mops, which is essential, otherwise blood loss might be underestimated.

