In the protocol outlined above, the risks are limited since the surgical procedure is identical to the one patients would undergo if not randomized to HIFU-AR. The only difference is that HIFU ablations are carried out on the section plane of the liver. These ablations will be performed only after final checking of the indication for them and immediately before the section phase. The duration of the HIFU ablations will last between 5 and 7 minutes. We consider that this minor increase in operative time will be compensated for by a major decrease in the time necessary to perform liver transection and haemostasis. A potential risk for HIFU-AR patients would be an injury to neighbouring organs secondary to HIFU ablations. Measures taken to avoid this include surgical mops placed under the targeted area to limit risks of ultrasound propagation. Furthermore, this risk was fully assessed during the phase I and IIa studies recently completed and no adverse effects were observed. The post-operative follow-up period will last 6 months, which seems to be sufficient to cover late adverse events. The study participants in the HIFU-AR group can expect to benefit from reduced blood loss and a decreased period of ischemia in the future liver remnant.

Based on previous preclinical and clinical experience, the proposed study design, and the safety monitoring plan described in this protocol, the sponsor considers that adequate risk mitigation measures are included in this protocol and that the benefit-risk profile is favourable.

To limit biases, blood losses are normalized by the resected hepatic area (in square centimetres), which allows to perform several types of anatomical hepatectomy. We also use stratification by surgeon to ensure equal allocation of subgroups of participants (i.e. to each surgeon) in each arm. The three surgeons ([name]) are trained with the HIFU prototype, as they already use it in an ongoing study [27].

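### Randomisation is stratified by surgeon but the stated primary test pools over surgeons; the test is valid, but turns conservative and forgoes some power if surgeons differ

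*Protocol article*

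**What the plan says.** Allocation (Study design): "The randomization will be performed via an Internet platform in the operating room and will be stratified by surgeon". The Discussion repeats this, "We also use stratification by surgeon to ensure equal allocation of subgroups of participants", and says that there are three surgeons, all trained on the device.

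Primary analysis (Statistical analyses): "A Wilcoxon (Mann-Whitney) rank-sum test will be used to compare the normalized blood loss distribution between the two arms at a 5% level". It is two-sided and run in the intent-to-treat and per-protocol populations. The Abstract and the Sample size section name the same test, the latter as "using a Wilcoxon (Mann-Whitney) rank-sum test with a 0.05 two-sided significance level". Surgeon is mentioned in none of these three places as part of the analysis.

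Target (Sample size): "the study will have 85% power to detect a twofold decrease of blood loss in arm A". The Discussion adds "we consider this twofold decrease clinically relevant". The Statistical analyses section plans means, standard deviations, medians and ranges for quantitative data, and names 95% confidence intervals for the positive-margin and local-recurrence rates. It names no between-arm estimate or interval for normalised blood loss.

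**The concern.** Balancing the arms within surgeon removes differences between surgeons from the comparison of arms. A test that ignores surgeon still counts those differences as noise, so its standard error is too large whenever surgeons differ. The true type I error then falls below 5%, and the trial does not collect the power that its own stratification has made available. With 42 patients that is worth having.

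This is more than a detail left open. The article fixes the primary test in three places without surgeon, so an analysis plan that adjusted for surgeon would have to depart from the published primary analysis.

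A second matter bears on how the result is read. The design rests on a twofold decrease and the stated next step is a phase III trial, but a rank-sum p-value gives no effect size.

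**Working it through.** **1. The plan's own figure.** Inputs from the Abstract and Sample size section: "Assuming a blood loss of 7.6 ± 3.7 mL/cm^2^ among controls" (the ± figure read as a standard deviation), a twofold decrease (7.6 to 3.8, difference 3.8), two-sided 0.05, power 85%, 1:1. The arm A standard deviation is not given; 3.7 is assumed. Noether's formula for the unstratified Wilcoxon test:

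- p = Φ(3.8 / (3.7 × √2)) = 0.766
- N = (1.960 + 1.036)² / (3 × (0.766 − 0.5)²) = 42.25 in total with unrounded p, or 21.1 per arm
- Power at N = 42: Φ(√126 × 0.266 − 1.960) = 84.8%

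The stated 21 per arm is reproduced, so sample size and named test agree with each other.

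**2. Why the pooled test is conservative.** Let ρ be the share of variance due to surgeon. With exact balance within surgeon, the variance of the arm difference is proportional to 1 − ρ, while the pooled test works with the full variance. Its true size is roughly 2Φ(−1.96 / √(1 − ρ)):

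- ρ = 0.10: 2Φ(−2.07) ≈ 3.9%
- ρ = 0.20: 2Φ(−2.19) ≈ 2.8%
- ρ = 0.30: 2Φ(−2.34) ≈ 1.9%

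Simulation with exact balance (7 per arm per surgeon, 40,000 runs) gives 3.8/2.8/1.8%. Uneven strata of 11/7/3 per arm give the same pattern.

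**3. Size and power with blocked allocation.** Simulation with 42 patients, three strata of 14, permuted blocks of 4, normal errors on the analysis scale, and the effect set so that the pooled test has about 85% power without a surgeon effect. Block size and ρ are assumptions.

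| ρ | Pooled size | Pooled power | van Elteren power | Surgeon-adjusted model power |
|---|---|---|---|---|
| 0 | 5.0% | 84% | 82% | 86% |
| 0.10 | 4.2% | 85% | 86% | 89% |
| 0.20 | 3.2% | 86% | 89% | 93% |
| 0.30 | 2.0% | 87% | 93% | 95% |

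Difference from the pooled test at ρ = 0/0.10/0.20/0.30: van Elteren −2/+1/+3/+6 points; adjusted model +2/+4/+7/+8 points. Blocks of 4 do not fill a stratum of 14 exactly, so the sizes lie slightly above those in step 2.

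**4. Sensitivity.** If surgeon effects are drawn at random in each run instead of being fixed, the conservatism is milder: pooled size 4.6/4.0/3.6% at ρ = 0.10/0.20/0.30. If the effect is 3.8 with standard deviation 3.7 (exact balance), pooled power is 88.7/89.2/90.2/91.5% and van Elteren 86.4/89.4/92.5/95.4% at ρ = 0/0.10/0.20/0.30.

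**5. What p < 0.05 shows.** With 21 per arm and standard deviation 3.7, significance on a t-approximation is reached at a difference of 2.021 × 3.7 × √(2/21) = 2.31 mL/cm², and 2.31 / 7.6 = 30%. In simulation, a true reduction of 33% is significant with the pooled test about 55% of the time.

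**The case against.** The strongest reply is that nothing fails. The pooled test is valid, its error is on the safe side, the 21 per arm was computed for this very test, and its power stays at about the planned 85% or above throughout. The surgeon share of variance is not in the article. One centre, one prescribed technique, three trained surgeons and normalisation by area are all reasons to think it small. If it is near zero, van Elteren is the weaker test. All of this stands, and it makes the point conditional.

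A reader might infer more than the document supports:

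- That the trial falls short of its planned power. It does not; what is forgone is power above plan, and only if surgeons differ.
- That the stratification shows an expected difference in bleeding between surgeons. The reason given is equal allocation of each surgeon's patients to the arms.
- That the trial cannot judge the twofold target. The planned means and medians, tabulated by arm, give an observed ratio; only its interval is unnamed. The twofold decrease is the effect to detect, not a threshold to be proved.
- That the unnamed interval is an error in itself. An article commonly leaves this to the full protocol or analysis plan, and the Analysis populations section refers to such a plan.
- That central venous pressure should also be a covariate, since "Central venous pressure (CVP) will be measured immediately before and after the transection". Its explanatory value would be a guess. HIFU comes immediately before section, so the planned arm A reading may follow it, and a reading before HIFU may be a new measurement.

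What does not fall away is that surgeon is in the randomisation and missing from the primary test as written.

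**Conclusion.** The mismatch between stratified allocation and a pooled primary test is real. It should be corrected, but it does not threaten the trial's validity. Its size depends on how much surgeons differ: negligible to small at a 10% share of variance, and at 20 to 30% a true size of about 3.2 to 2.0% with 3 to 6 points of power forgone against van Elteren, or 7 to 8 against an adjusted model. These figures rest on the assumed surgeon shares, equal strata, blocks of 4, fixed surgeon effects and normal errors. The direction does not depend on the exact strata or on whether surgeon effects are fixed or random. The ratio with its interval is recommended because a significant test is compatible with reductions well short of twofold.

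**What to change.** In the Statistical analyses section, make the primary analysis account for surgeon by one of two routes, chosen before outcome data are seen:

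- the van Elteren (surgeon-stratified Wilcoxon) test; or
- a linear model on log normalised blood loss with arm and surgeon.

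In either case report the arm A/arm B ratio of normalised blood loss with its 95% confidence interval. If van Elteren is chosen and the interval comes from the log model, say which of the two governs the conclusion, because they can disagree. Keep the pooled Wilcoxon test as a sensitivity analysis.

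The change is one of wording: surgeon is already recorded for the randomisation, and neither new data nor a change to the 42 patients is needed. Van Elteren costs about 2 points of power if surgeons do not differ. The adjusted model costs none under normal errors on the log scale, but depends on that assumption more than a rank test does.

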In both arms, the secondary endpoints are:transection time (minutes) defined as the time required to achieve the liver transection (minutes) and the transection time per surface of resected liver area (minutes/square centimetres);haemostasis time (minutes), defined as the time lapse between the end of transection until completion of haemostasis (minutes);clip density on the section area, defined as the total number of haemostatic clips used to perform haemostasis on the liver section area divided by the raw surface of the remaining liver (in square centimetres) (number of clips per square centimetre of liver area);rate and duration of the Pringle manœuvre, defined as the number of patients requiring Pringle’s manœuvre during the operating procedure [if blood loss > 500 mL during the transection, measured through the suction device, the surgeon will be authorized to perform a hepatic pedicular clamping (Pringle’s manœuvre)];rate of patients needing a blood transfusion, defined as the number of patients requiring blood transfusions either during the operation or after it (per-operative transfusion will be required for patients with blood loss > 1000 mL; post-operative transfusion will be required if Hb <8 g/dL or 10 g/dL if previous history of coronary disease or stroke);duration of hospital stay (days), calculated from D_0_ (date of surgery) to the end of hospitalization post-surgery;safety and tolerability assessed using the Dindo-Clavien classification specific to surgical complications. During the first 10 days after surgery, we will collect data on haemoglobin, platelets, alanine amino-transferase (ALT), aspartate amino-transferase (AST), gamma-glutamyltransferase (GGT), prothrombin time (PT) and total bilirubin values;the proportion of patients with malignant tumours who have a positive resection margin and patients with local recurrence (from randomization to M_6_).

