### Study population

Inclusion and exclusion criteria are listed in Table 1.

**Table 1 Tab1:** Inclusion and exclusion criteria

Inclusion criteria	Exclusion criteria
Age ≥ 18 years	History of previous major hepatic surgery (i.e. more than three liver segments) or biliary major surgery (except gall-bladder surgery by laparoscopy if more than 6 months previously)
Patients with liver metastases requiring a hepatectomy of ≥ 2 segments	Patients with cirrhosis or sinusoidal obstruction syndrome with portal hypertension
Eastern Cooperative Oncology Group performance status ≤ 1	Pregnant women
Adequate bone marrow and liver function at baseline (defined by platelet count ≥ 100 × 10^9^/L, and haemoglobin of ≥ 9 g/dL, and total bilirubin ≤ 1.5 × upper limit of normal, and transaminases ≤ 5× upper limit of normal)	
Recovered from prior anti-neoplasic treatment-related toxicity (grade <2 persistent treatment-related toxicity as per Common Terminology Criteria for Adverse Events v4 are accepted	
Willingness for follow-up visits	
Covered by a medical insurance	
Signed and dated informed consent indicating that the patient has been informed of all aspects of the trial prior to enrolment	

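### Post-operative laboratory values fall under an unadjusted rank-sum test although baseline values of most of them are already measured: a valid test that gives up some power, and a free improvement

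*Protocol article*

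**What the plan says.** Under Objectives, the secondary endpoint on safety is described as "safety and tolerability assessed using the Dindo-Clavien classification specific to surgical complications". The same item then says: "During the first 10 days after surgery, we will collect data on haemoglobin, platelets, alanine amino-transferase (ALT), aspartate amino-transferase (AST), gamma-glutamyltransferase (GGT), prothrombin time (PT)". The last analyte in that list is bilirubin.

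Under Statistical analyses, the general rule is: "For secondary endpoints, data will be compared between the two arms using a Wilcoxon (Mann-Whitney) rank-sum test". Positive margin and local recurrence are to be given as proportions with 95% confidence intervals, and post-operative complications are to be tested by Pearson's chi-squared or Fisher's exact test. The laboratory values have no rule of their own.

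On baseline, Data collection and follow-up requires "complete physical examination and laboratory tests within 7 days before randomization". Table 1 (Study population) sets minimum platelet and haemoglobin levels and also requires "total bilirubin ≤ 1.5 × upper limit of normal, and transaminases ≤ 5× upper limit of normal". The Statistical analyses section says that baseline biological data will be summarised and gives them no further use.

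**The concern.** A two-sample rank-sum test takes no covariate. If a patient's pre-operative value predicts the post-operative value, that predictable part stays in the noise although the trial already holds the information to remove it. Randomisation is stratified by surgeon only, so the design does not balance baseline laboratory values among 42 patients.

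What is at stake is sensitivity. These values are the quantitative liver and blood data of a small trial of a device without a CE mark, for which a phase III study is the planned next step. A real difference between arms is easier to miss than it needs to be.

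**Working it through.** **Inputs.** 21 patients per arm, two-sided alpha 0.05, control blood loss 7.6 with SD 3.7 mL/cm², a halving (difference 3.8), 85% power (all from Sample size). The correlation rho between baseline and post-operative values is not in the documents; it is assumed and shown from 0 to 0.7.

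**1. The plan's own figure.** Noether's formula for the rank-sum test:
- p = Φ(3.8 / (3.7 × √2)) = 0.766
- N = (1.960 + 1.036)² / (3 × (0.766 − 0.5)²) = 42.25 with unrounded p, or 21.1 per arm; power at 42 is 84.8%.

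The stated 21 per arm reproduces. It was sized for blood loss, so the power for laboratory values is whatever 21 per arm happens to give.

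**2. What adjustment does in theory.** Adjusting for baseline multiplies the residual variance by 1 − rho². The difference detectable with 80% power (normal approximation) is (1.960 + 0.842) × √(2/21) × √(1 − rho²) SD:

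| rho | variance factor | detectable difference |
|---|---|---|
| 0 (same as unadjusted) | 1.00 | 0.87 SD |
| 0.3 | 0.91 | 0.83 SD |
| 0.5 | 0.75 | 0.75 SD |
| 0.7 | 0.51 | 0.62 SD |

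**3. Simulated power.** Bivariate normal baseline and post-operative values, 21 per arm. Rank analysis of covariance is a regression of outcome ranks on arm and baseline ranks.

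| difference | rho | rank-sum | rank analysis of covariance |
|---|---|---|---|
| 0.9 SD | 0 | about 79% | about 79% |
| 0.9 SD | 0.3 | about 79% | about 82% |
| 0.9 SD | 0.5 | about 79% | about 88% |
| 0.9 SD | 0.7 | about 79% | about 95% |
| 0.6 SD | 0 | 46% | 45% |
| 0.6 SD | 0.3 | 47% | 49% |
| 0.6 SD | 0.5 | 46% | 54% |
| 0.6 SD | 0.7 | 45% | 70% |

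With no true difference, both methods reject in about 5% of trials at every rho.

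**4. Change from baseline is not a safe substitute.** A rank-sum test on simple change, for a 0.6 SD difference, has 26% power at rho 0 (against 46% for the unadjusted test), 44% at rho 0.5 (against 46%) and 67% at rho 0.7 (against 45%). It loses badly when rho is low. Rank analysis of covariance does not.

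**5. Chance imbalance.** With 21 per arm the standard error of a baseline difference is √(2/21) = 0.309 SD. A gap above 0.5 SD in either direction therefore has probability 2 × (1 − Φ(0.5/0.309)), about 10.5% per analyte. Given a gap of exactly 0.5 SD and no device effect, the rank-sum test rejects in about 8% of trials at rho 0.5 and 12% at rho 0.7; the adjusted test stays near 5%. Averaged over all randomisations the rank-sum test is still at 5%.

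**The case against.** The strongest reply is that the article never says in terms that the laboratory values will be tested. The safety item names the Dindo-Clavien classification as the instrument and says only that laboratory data will be collected. The rank-sum sentence is generic and cannot be literal for every secondary endpoint, since the rates of transfusion and of Pringle use are binary. No peak, nadir or day is fixed, and how ten days of laboratory data are summarised is normally a matter for the analysis plan. This stands in part: the rank-sum test reaches these values by inference from a general sentence. But that sentence names a test, the laboratory values sit inside a secondary endpoint, and no exception is made for them. An analysis plan that follows the article would inherit the unadjusted test.

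Several stronger readings are tempting, and the documents do not support them:
- **That the test is biased or invalid.** It is not. Under randomisation its 5% error holds; the figures under chance imbalance are part of that 5%.
- **That the entry limits prove a strong correlation.** Table 1 gives bounds for eligibility. It gives neither the spread among enrolled patients nor rho. Major resection may dominate the post-operative values, and transfusion may weaken the link for haemoglobin.
- **That every listed analyte has a baseline value.** Table 1 supports haemoglobin, platelets, total bilirubin and transaminases. Baseline GGT and prothrombin time are not confirmed.
- **That the article names liver failure as a harm of HIFU.** The phrase "liver ischemia–reperfusion injury, which is known to predispose patients to post-operative liver failure" in the Discussion concerns clamping of the hepatic pedicle. The device risk it names is injury to neighbouring organs.

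Harm detection also does not rest on this test alone: there are safety board meetings after 6, 12 and 24 randomised patients, steering committee review of grade 3 or higher events, and graded complications.

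**Conclusion.** The point holds as a loss of efficiency in a secondary analysis. For a 0.9 SD difference with 21 per arm, adjustment adds nothing at rho 0, about 3 points of power at rho 0.3, about 9 at rho 0.5 and about 16 at rho 0.7. The size rests on an assumed rho, which may differ by analyte, and on normally distributed data in the simulation. It also assumes that the laboratory values are in fact compared between arms under the general sentence. Nothing stated is wrong, and the trial's main conclusion does not depend on it. It is a minor, free improvement.

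**What to change.** In Statistical analyses, add wording such as: Where post-operative laboratory values are compared between arms, one pre-specified summary per analyte over the first 10 days (for example the lowest haemoglobin and platelets, and the highest ALT, AST and total bilirubin) will be compared by rank analysis of covariance, with the pre-randomisation value of the same analyte as covariate. GGT and prothrombin time will be handled in this way only if a baseline value is collected.

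Summary and method should be fixed before the data are seen, with one method for all analytes. The cost is a few lines of text and code, one degree of freedom per model, and the loss of any patient whose baseline value is missing. No new data are needed.
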